## Abstract

**Background:**

Total knee arthroplasty (TKA) is effective in reducing pain and improving function for end-stage knee osteoarthritis. However, muscle weakness and functional limitations persist despite assistance from post-operative rehabilitation programs that traditionally focus on quadriceps strengthening and range of movement exercises. Hip abductor muscle weakness is evident in knee osteoarthritis and hip muscle strengthening reduces knee pain in this group. Following TKA, people with weak hip abductor strength perform more poorly on measures of physical function. However, very little is known of the effectiveness of including hip abductor strengthening exercises in post-operative rehabilitation. The aim of this trial is to compare the effects of targeted hip abductor strengthening to those of traditional care in a TKA rehabilitation program on muscle strength, patient reported outcomes and functional performance measures.

**Methods/design:**

This protocol describes a single-blinded randomized controlled trial, where 104 participants referred for inpatient rehabilitation following TKA will be recruited. Participants will be randomized using computer-generated numbers to one of two groups: usual care or usual care with additional hip strengthening exercises. Participants will attend physiotherapy daily during their inpatient length of stay, and will then attend between six and eight physiotherapy sessions as an outpatient. Primary outcomes are isometric hip abductor strength and the Knee Injury and Osteoarthritis Outcome Score (KOOS). Secondary outcomes are stair climb test, 6 min walk test, timed up and go, 40 m fast-paced walk test, 30 second chair stand test, isometric quadriceps strength, Lower Extremity Functional Scale (LEFS) and SF-12. Outcome measures will be recorded at baseline (admission to inpatient rehabilitation), and then 3 weeks, 6 weeks and 6 months post admission to rehabilitation.

**Discussion:**

The findings of this study will determine whether the addition of targeted hip strengthening to usual care rehabilitation improves physical performance and patient reported outcomes following TKA when compared to usual care rehabilitation. This will then determine whether targeted hip strengthening exercises should be included in traditional rehabilitation programs to improve the outcomes following total knee arthroplasty.

**Trial registration:**

The trial protocol was registered with the Australian Clinical Trial Registry (ACTRN12615000863538) on 18 August 2015.

**Electronic supplementary material:**

The online version of this article (doi:10.1186/s12891-016-1104-x) contains supplementary material, which is available to authorized users.

## Background

End-stage knee osteoarthritis (OA) is a significant health issue worldwide resulting in severe pain and disability [1, 2]. Total knee arthoplasty (TKA) leads to significant improvements in pain and the performance of functional activities such as walking for patients with end-stage knee OA [3]. Improvements in pain and functional performance are achieved with assistance from rehabilitation programs [3–6]. Traditional rehabilitation programs typically focus on improving knee strength and range of movement, and improving gait and stair climbing [7–10]. For most programs, emphasis is placed on achieving optimal knee range of movement and improving quadriceps muscle strength [11].

Despite completing traditional rehabilitation programs, functional limitations persist in patients following TKA compared to healthy age-matched individuals. Following TKA, people have reduced walking speed, and report difficulty climbing stairs and rising from a chair [12, 13]. They also perform more poorly on tests of Timed Up and Go (TUG) and stair climbing times than healthy adults [3, 13]. The persistence of functional limitations demonstrates that there is a need to expand on the focus of current rehabilitation practices to restore the function of patients following TKA to the levels of healthy adults.

Prior to surgery, patients with end-stage knee OA demonstrate reduced hip abductor strength [14]. They exhibit altered gait patterns that may be an attempt to avoid knee pain, to minimize forces through the affected cartilage, or to reduce the sensation of the knee giving way [15]. Consequently, patients with severe knee OA walk with decreased gait speed, reduced stride length, and increased time in double limb support [16]. These factors combined with reduced activity may result in lowered activation and diminished strength of the hip abductors over a period of time [17]. There has been a small quantity of research with promising findings that targeted hip strengthening programs in patients with end stage knee OA may lead to improvement in symptoms and quality of life [18, 19].

Although often ignored in post-operative rehabilitation programs, there is sufficient evidence that the hip abductor weakness present prior to surgery continues after TKA and is not improved with current rehabilitation interventions [20, 21]. Post-operative pain, reduced demands on the operated limb in the early post-operative period and habitual gait patterns are also likely to contribute to further reductions in hip abductor strength. Following TKA, there is a correlation between hip abductor strength and functional outcomes [20, 21]. Hip abductor strength contributes to physical function such as turning whilst walking and rising from a chair in people with unilateral TKA. There is a correlation between stronger hip abductor muscles and faster times for TUG and stair climb tests [20, 21]. Unless rehabilitation programs specifically include hip abductor strengthening exercises, it is unlikely that the hip abductors will return to normal levels of strength, contributing to ongoing difficulties in activities of daily living such as walking and stair climbing. Given the improvement in strength seen in pre-operative patients, it is likely that similar rehabilitation efforts will yield improvements in function post-operatively. Despite this, no study has investigated the effects of hip abductor strengthening on improving strength or function following TKA.

The aim of this randomized controlled trial (RCT) is to compare the effects of targeted hip abductor strengthening with those of traditional care in a TKA rehabilitation program on muscle strength, patient reported outcomes and functional performance measures.

## Methods/design

### Trial design

The study design is a single-blinded randomized controlled trial (Fig. 1) adhering to Standard Protocol Items: Recommendation for Interventional Trials (SPIRIT) guidelines [22]. Outcomes will be measured at admission to inpatient rehabilitation, and at 3 weeks, 6 weeks and 6 months following the commencement of rehabilitation. These time points were chosen to adequately measure the rate of improvement in all outcome measures.

**Fig. 1 Fig1:**
[figure not shown]
Flow diagram of study protocol

The trial protocol was registered with the Australian New Zealand Clinical Trials Registry (ANZCTR number: 12615000863538) on 18 August 2015. Ethical approval was granted by La Trobe University Faculty Human Ethics Committee (FHEC 14/256). Reporting of the RCT will follow the CONSORT guidelines for randomized trials of nonpharmacologic treatment (Fig. 1) [23].

### Participants

A sample of 104 males and females with primary unilateral TKA will be recruited between October 2015 and March 2017 from a 90 bed private rehabilitation hospital that treats patients following joint replacements, multi-trauma, stroke, cardiac surgery and general deconditioning.

Participants will be eligible if they are aged 50 years or older, have had a primary unilateral TKA for end-stage knee osteoarthritis in the previous two weeks and are admitted for inpatient rehabilitation followed by outpatient rehabilitation.

Participants will be excluded in the presence of unstable medical conditions preventing the patient from participating in the rehabilitation programs, history of ipsilateral hip replacement, ipsilateral hip osteoarthritis or lateral hip pain, neurological or any other conditions affecting strength or function of lower limbs. Eligibility of prospective patients will be identified on their admission to inpatient rehabilitation from the acute hospitals by the treating physiotherapists.

### Randomisation and allocation concealment

Eligible patients will be identified by the treating physiotherapist. The treating physiotherapist will inform the patient of the study, give them the patient information sheet and arrange for a meeting with the primary researcher. The primary researcher will discuss any questions with the patient and gain informed consent of willing participants. Eligible patients will be randomized by a computer-generated list of random numbers to usual care or usual care plus hip strengthening. An independent person, not involved in delivering the intervention or testing, will manage the allocation list and numbered opaque envelopes containing the allocated group of each participant. Only the treating physiotherapist will be informed of the group allocation of the participants. The allocation list will not be available to the researchers and the participants will not be informed which group they are in. The participants will be informed that there are two different rehabilitation programs but will not be told that one program is specifically targeting hip strengthening exercises. This is to prevent potential bias from knowledge of treatment. The rehabilitation will be conducted in a large busy gym where there are many different patients with different diagnoses treated at the same time by their individual physiotherapists with individual exercise programs dependent on each patient’s needs. This will reduce the probability of patients from one intervention seeing the other intervention group’s exercises. A survey on exit from the study will be conducted to determine which group the participants thought they were in during their rehabilitation.

### Procedure

Baseline and all follow-up assessments will be performed in the physiotherapy department at the rehabilitation hospital by a blinded assessor. The assessments of isometric muscle strength, knee range of movement, step tap test and 30-second chair stand test will be conducted in a closed private treatment room in the physiotherapy department. The Timed Up and Go Test and Stair Climb Test will be assessed in a corner of the gym away from the patient treatment area. The 6-minute walk and 40 m Fast-paced Walk will be assessed along a premeasured 50 m-long walkway located on the other side of the hospital. This will prevent the assessor from observing the interventions and the treating physiotherapists observing the assessments. All participants will attend daily physiotherapy for their length of stay as an inpatient, and will then attend between six and eight physiotherapy sessions as an outpatient. All participants will be given a home exercise program on discharge from inpatient rehabilitation. All participants will attend weekly outpatient physiotherapy sessions and during these sessions, the home exercise program will be progressed.

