### Performance quality

Performance quality will be monitored by the physiotherapist. The physiotherapist will reassess each participant at the start of each session, and the exercises modified accordingly. If there are significant increases in pain (Visual Analogue Scale = 5 or greater) the physiotherapist will use his/her clinical reasoning to reduce intensity of particular aggravating exercises or add specific manual physiotherapy treatment as required. To ensure that appropriate muscle adaptation is achieved, the participant’s exercises will be progressed according to the American College of Sports Medicine (ACSM) guidelines [28] as soon as the patient is able, and details and criteria for this progression are described in the Additional file 1.

The treating physiotherapist will record the details of each treatment session, and will include the type of exercises and dosage. Any changes to the exercises or adverse responses will be noted. Following discharge from inpatient rehabilitation, participants will be given a home exercise program to continue their exercises and a diary to record daily exercises. The exercises will be progressed during the outpatient phase and the diary used to record dosage and completion of exercises. On discharge from outpatient rehabilitation, the participants will continue to complete the home exercise program until the 6-month follow-up.

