### Outcome measures

Demographic information to be collected from all participants includes: name, age, gender, height, weight and body mass index. The type of prosthesis used (including patella resurfacing), left/right TKA, previous joint replacements, co-morbidities, social history (including place of accommodation, occupation/retired), co-interventions (e.g. hydrotherapy), length of hospital stay, number of treatment sessions and analgesics used will be recorded.

The measures that will be used to assess outcome are summarized in Table 4. The primary outcomes measures are: Knee Injury and Osteoarthritis Outcome score (KOOS) and isometric hip abductor muscle strength. The secondary outcome measures are: Stair Climb Test, 6 min walk test, Timed Up and Go, 40 m fast-paced walk test, 30-second chair stand test, step test, isometric quadriceps muscle strength, Lower Extremity Functional Scale (LEFS) and SF-12. These physical performance measures were selected based on the recommendations from Osteoarthritis Research Society International (OARSI) for older patients (>40 years old) diagnosed with hip and/or knee OA [29].

**Table 4 Tab4:** Outcome measures

Outcome	Measurement
Knee Injury and Osteoarthritis Outcome Score	Pain, other symptoms, function and quality of life
Isometric strength of hip abductors	Hand held dynamometer (Newtons)
Stair climb test	Total time (sec) to ascend and descend 4 steps.
6 min walk test	Distance (m) walked in 6 min
Timed Up and Go	Timed rise from chair, walk 3 m and return to sitting position.
40 m fast-paced walk test	Time (sec) taken to walk 40 m
30-second chair stand test	No. of sit-to-stands performed in 30 seconds
Step test	Number of step taps on a step in 15 seconds
Isometric strength of quadriceps	Hand held dynamometer (Newtons)
Knee ROM	Goniometer (degrees)
Lower Extremity Functional Scale	Lower extremity functional status
SF-12	Overall Health
Other measures	
Compliance	Therapist treatment records and patient diary
Adverse effects	Therapist treatment records and patient diary
Type of TKR	Operation report or surgeon contact

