Primary and secondary outcomes will be measured at admission to inpatient rehabilitation (approximately 7 days post-operatively), 3 weeks, 6 weeks and 6 months after commencing the rehabilitation program. A discrepancy is often reported in the recovery of patient reported outcomes compared to functional performances, with the more rapid improvement noted in patient reported outcome scales while functional performance measures are often significantly reduced in the early post-operative period [30]. Therefore, the two types of outcome measures have been included to ensure an accurate representation of rehabilitation outcomes following TKA.

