### Primary outcome measures

#### Knee injury and osteoarthritis outcome score (KOOS)

The Knee Injury and Osteoarthritis Outcome Score (KOOS) is a self report questionnaire with 42-items in 5 separately analyzed subscales of pain, other symptoms, function in daily living, function in sport and recreation, and knee–related quality of life [31]. The tool has good test-retest reliability with ICC _(2,1)_ values in 26 patients 6 months post TKA of 0.73 (QOL), 0.74 (Sport/recreation), 0.82 (ADL), 0.85 (Symptoms), and 0.94 (Pain). Good content validity demonstrated by 90 % of patients who regarded improvement in the subscales Pain, Symptoms, Activities of Daily Living, and knee-related Quality of Life to be extremely or very important when deciding to have their knee operated on. The KOOS is responsive on all subscales particularly the knee-related Quality of Life subscale (effect size 2.86 at 6 months post TKA and 3.54 at 12 months post TKA) [32].

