#### Data and statistical analysis

An estimate of sample size was made on the ability to detect a medium effect (Cohen’s f = 0.25). The assumption of obtaining a medium effect size was reasonable based on the effect sizes reported for similar measures such as the WOMAC by other studies in the literature (effect size for WOMAC function = 0.3, WOMAC pain = 0.31) [18]. A standard statistical package was used [78]. To obtain a power of 0.8 at a significance level of α = 0.05, a minimum sample of 82 participants would be needed. To allow for loss to follow-up the aim was to recruit a sample of approximately 104 participants.

Participant characteristics and baseline data will be summarized by descriptive statistics. Independent sample t-tests for parametric data (or a chi-squared test for categorical data) will be used to determine the comparability of the two groups at baseline on measures of age, gender and BMI. All data will be analysed using intention to treat principles. Any missing data will be replaced by the last observation carried forward. Repeated measures ANOVA (group by time) calculations will be used to determine the main effects and interactions of group (hip abductor strengthening vs usual care exercises) and time (repeated factor: baseline, 3 weeks, 6 weeks, 6 months) for all outcome measures. Statistical analysis will be completed using SPSS software (version 22) and the significance level set at *P <* 0.05.

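### A missed on-site visit loses KOOS, a self-report primary outcome that could be collected remotely, and the plan then carries forward an earlier post-operative score

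*Protocol article*

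**What the plan says.** All from the protocol article.

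- **Place of assessment (Procedure):** "Baseline and all follow-up assessments will be performed in the physiotherapy department at the rehabilitation hospital by a blinded assessor". The section then assigns rooms or areas to the strength, range-of-movement, balance, stair and walking tests. It gives no other route for the questionnaires.
- **Primary outcomes (Outcome measures):** "The primary outcomes measures are: Knee Injury and Osteoarthritis Outcome score (KOOS) and isometric hip abductor muscle strength".
- **Nature of KOOS (its own section):** it "is a self report questionnaire with 42-items in 5 separately analyzed subscales". LEFS is likewise described as self-report, and SF-12 as a generic measure of the patient's well-being.
- **Timing (Outcome measures):** "Primary and secondary outcomes will be measured at admission to inpatient rehabilitation (approximately 7 days post-operatively), 3 weeks, 6 weeks and 6 months" after rehabilitation starts.
- **Treatment contact (Procedure):** after the inpatient stay, participants "will then attend between six and eight physiotherapy sessions as an outpatient", attending weekly.
- **Home recording (Performance quality):** "participants will be given a home exercise program to continue their exercises and a diary to record daily exercises".
- **Loss and missing data (Data and statistical analysis):** a minimum of 82 is needed; "To allow for loss to follow-up the aim was to recruit a sample of approximately 104 participants". Analysis is by intention to treat, and "Any missing data will be replaced by the last observation carried forward".

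**The concern.** The dynamometer, stair and walking tests need the participant on site. A questionnaire does not. The Procedure section nevertheless ties both to the same visit, so one missed visit removes a primary outcome that needs no equipment.

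The visit most exposed is the 6-month one. The 3-week and 6-week assessments fall during or close to treatment contact, whereas by 6 months there is no therapy session to combine with the trip.

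Non-attendance may well be related to outcome: pain, poor function or a good recovery could each keep someone away, and the reasons could differ between arms. Extra recruitment protects precision, not against selective loss. Because the plan carries the last value forward, a missed 6-month KOOS becomes a score from the first weeks after surgery, possibly the admission score at about day 7. Whether that imputation rule is suitable is a separate question. The point here is that the real value could often be obtained, and then nothing need be imputed.

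**Working it through.** **1. The plan's own figures.** Inputs from Data and statistical analysis: f = 0.25, power 0.80, α = 0.05, N = 82, recruit about 104. For the between-group effect in a repeated-measures ANOVA with m = 4 time points and an assumed within-person correlation ρ = 0.5 (the article gives none):

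λ = f²·N·m / [1 + (m − 1)ρ] = 0.0625 × 82 × 4 / 2.5 = 8.2, with 1 and 80 degrees of freedom.

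This gives power 0.808, and 82 is the smallest even N that reaches 0.80. The implied loss allowance is (104 − 82)/104 = 22/104 = 21.2%. The article states no rate; this one is inferred.

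**2. Gap between last therapy session and the 6-month visit.** Outpatient care starts about one week after discharge and runs for six to eight weekly sessions. Length of stay is not given; assume 1 to 2 weeks.

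- Shortest: 1 week stay + 1 week, first session at week 2, sixth at week 7.
- Longest: 2 weeks stay + 1 week, first session at week 3, eighth at week 10.

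Six months is about week 26, so the visit comes 16 to 19 weeks after the last session, about four months.

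**3. Effect of carrying forward.** Take d = 2f = 0.50 as the true 6-month difference. Assume no group difference at baseline, the same effect in those lost as in those seen, an unchanged SD, and equal loss p in both arms. If those lost contribute an earlier difference δ:

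observed d = (1 − p) × 0.50 + p × δ, with p = 22/104.

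| Value carried forward | δ | Observed d |
|---|---|---|
| Baseline only | 0 | 0.39 |
| Earlier visit with half the final difference (assumed) | 0.25 | 0.45 |
| Earlier visit with the full difference | 0.50 | 0.50 |

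So 0.39 is the unfavourable end. It applies only if everyone lost has no KOOS after baseline.

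**4. What remote collection would recover in the baseline-only case.** Assume half to three quarters of the 22 return the questionnaire.

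- Half: 11 still missing; 0.50 × 93/104 = 0.45.
- Three quarters: 5.5 still missing; 0.50 × 98.5/104 = 0.47.

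**5. Unequal loss between arms.** The KOOS section cites an effect size of 2.86 at 6 months for the quality-of-life subscale. If a change of that size were replaced by no change in 5 or 10 percentage points more of one arm, the contrast would move by 0.05 × 2.86 = 0.14 or 0.10 × 2.86 = 0.29 SD. This is a rough illustration: the baseline behind the cited figure may not be the day-7 baseline of this trial, and the other subscales may change less.

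**The case against.** **The article is condensed, and the full protocol may describe retrieval of missed questionnaires.** This has some force. But the complaint does not rest on silence: the Procedure section says where all follow-up takes place, and a home route would need an exception to that sentence.

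**The paragraph is about setting and blinding of physical tests.** True, every test it places is a physical one, and KOOS is reached only through the general wording. Yet no other place or route is given for KOOS. The blinding rationale, keeping assessor and therapists from seeing each other's work, gives no reason to keep a questionnaire on site.

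**Stopping therapy is not missing an assessment.** This stands. A reader might infer that anyone who stops physiotherapy drops out of outcome collection. The article does not say so: assessments are timed from the start of rehabilitation and the analysis is by intention to treat. Someone who has stopped therapy may still attend.

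**The size could be overstated.** This also stands. A reader might calculate the gain in precision from analysing 93 to 98 rather than 82 people, or a bias among attenders only. Both presuppose a complete-case analysis, whereas the plan keeps everyone in through carried-forward values. Nor is 21% a stated forecast, and some of those lost will have withdrawn or be unreachable.

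**One supervised mode is a defensible choice.** Mixed modes could introduce a small difference, concentrated in those who miss visits. That is a real cost, but a smaller one than substituting a score from weeks or months earlier.

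**Conclusion.** The point holds in a limited form. The article's on-site rule covers all follow-up, so a missed assessment visit costs KOOS, LEFS and SF-12 as well as the physical tests, and the analysis section then substitutes an earlier post-operative score. The exposure is mainly at 6 months.

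With the inferred 21% loss, a true d of 0.50 would be seen as about 0.39 if all those lost had only baseline carried forward. It would be closer to 0.50 if later scores were available and already showed the group difference. Unequal loss between arms could shift the contrast further, in either direction. These figures depend on the assumptions listed and are not forecasts.

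This is a cheap improvement to data collection. It is not a contradiction in the document, does not change the required sample size, and does not help the other primary outcome, hip abductor strength, or the performance tests.

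**What to change.** Amend the Procedure section so that:

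- strength, range-of-movement and performance tests stay on site with the blinded assessor;
- KOOS, LEFS and SF-12 are collected by post, online or telephone whenever an assessment visit is missed, above all at 6 months, and including after therapy has stopped, unless the participant withdraws consent to follow-up;
- any telephone completion is done by the blinded assessor or another existing team member unaware of allocation;
- the mode of completion is recorded for each questionnaire.

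The cost is a short amendment, some postage or calls, and a small mode difference in a minority of participants. Participants already keep an exercise diary at home, so self-recording away from the hospital is not new to this trial. No new staff are needed.
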